#### Validation of determinants

The determinants will be determined using the systematic review and local qualitative study described in the first step. An initial list of determinants will be developed and will be then graded based on the relevance (strong association with behavior) and variability (impact of educational intervention on determinants). Also, we will perform a number of ways to prioritize these determinants. First, a broad search will be conducted in all valid databases to relate the determinants with the smoking cessation behavior using related keywords. After prioritizing the determinants based on the literature review and cross-sectional study, the views and opinions of potential participants of the program will be examined through a focused group discussion. The opinions of participants will be applied; and then, the variability, importance, and relevance of determinants of HS will be addressed in an expert panel meeting. We will also conduct a cross-sectional study to more closely explore the determinants of HS, which are described below in detail. After summarizing the comments and results of the cross-sectional study, the determinants will be prioritized and approved.

Validation of the matrix of change goals: The matrix of change goals will be designed based on the opinions and ideas of the experts and potential participants of the program. These goals will be confirmed by the research team during two to three sessions after being edited and reviewed.

The product of second step will be designing the intervention objectives.

### Step 3: Choosing theory-based approaches and practical strategies

Once the change objectives will be identified; we will use IM to identify methods that have sufficient and effective impacts on those objectives. Therefore, we will use appropriate and relevant theoretical and practical methods, which will be determined in a number of ways. First, we will have a comprehensive overview of all theories of health education and health promotion to determine the appropriate theoretical and practical approaches to the determinants. For example, what will be proposed by the theoretical and practical methods to change the knowledge in scientific texts? In the next step, these theoretical and practical approaches will be sent to five health education experts with experience in the field of behavior change theories. After applying the experts’ comments, these methods will be communicated to potential program participants, and in a focus group discussion we will be sure that these methods are in line with the beliefs and culture of the target group. After gathering the opinions of experts and women in the target group, they will be reviewed again at the expert panel meeting; and if necessary, they will be revised.

#### Quality contro**l** of “choosing theory -based approaches and practical strategies”

The theoretical and practical approaches affecting the change objectives will be identified on the basis of empirical evidence, extensive review of behavior change theories, and opinions of experts and potential program participants. Based on the theoretical and practical approaches, the scope, sequence, and context of the program will be determined to some extent, and these will be considered as the products of third step.

### Step 4: Developing the intervention

At this step, the main material of the program will realistically be produced. These will include program content, activity sequences, messages, presentation channels, and scheduling. Before producing the program material, some documents will be designed. These documents, which include the complete project information such as project duration, goals, budget, list of change objectives, and theoretical and practical methods; will be useful guides to produce the program materials. Messages and program materials will be produced based on the designed documents. It should be noted that, budget and time frame will be taken into account in designing the program materials. After performing the initial design of the program, the materials will be reviewed during a meeting with ten potential program participants to ensure that messages and presentation channels are accepted. After applying the audience feedbacks, the research team will discuss the design of the program during an expert panel meeting, and will revise it if needed. Prior to the actual implementation of program, the materials will be examined in a small sample group to ensure that they are sufficiently acceptable and executable.

#### Quality control of the intervention development process

At this stage, the researcher will invite the participants to obtain their views on the components and materials of the program; and based on their views and cultural issues, the materials and components of the program will be revised. At first, five training sessions will be held on theoretical approaches and practical applications for women and those who have influence on them. Each session is estimated to take 90 min and will be held once a week. Materials and components of the program will be reviewed.

### Step 5: Planning the implementation of the program

In this study, the fifth IM step, which involves planning to implement the program, will not be taken in detail until the first evaluation study will be executed. From the beginning of the program, the research team will be composed of a mix of potential program participants and implementers, who will be involved at all stages of the program design. Also, their ideas and comments will be used in all parts of the program. The produced materials will be pre-tested prior to actual large-scale implementation of the program to ensure adequate adoption and implementation of the program.

### Step 6: Planning the evaluation

Evaluating each one of the intended health outcomes, behavioral and environmental determinants, and change objectives of HS will be addressed by designing evaluation questions and taking into account the budget and time frame. In this step, we will review the logical pattern of change and design evaluation questions based on determinants, behavioral and environmental goals, change objectives, and outcomes. We will then evaluate the effectiveness of designed program in a quasi-experimental study. The purpose of quasi-experimental intervention will be evaluating the effectiveness of designed educational intervention on smoking cessation/reduction rate among women.

The target population in this study will be all 15 years old women and older in Bandar Abbas.

#### Sample size

To calculate the sample size in this semi-experimental study, the sampling formula in comparative studies will be used, considering (d = 1, s1 = 2.55 and s2 = 2.38, respectively) based on the findings of similar studies (self-efficacy three months after training in both intervention and control groups in the study of Ahmed Sotoudeh), [26]. Also, considering the errors of α = 0.05 and β = 0.2 (power of 80%), the sample size will be calculated as 96 individuals in each group. However, by taking 10% sample drop into account, the number of samples in each group will be estimated as 106 individuals.

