#### Instrument

The measurement tool will be similar to the final version of questionnaire, which will be designed based on the matrix (change, determinants, and practical objectives). The questionnaire will consist of two parts as follows: demographic information, and change objectives and expected outcomes of the program. The validity and reliability of the questions will be examined by the opinions of a number of experienced experts in this field.

*The measurement of primary outcomes* (1) level of hookah cessation immediately after the intervention, (2) level of hookah cessation within 3 months of the intervention, (3) level of hookah cessation within 6 months of the intervention, and (4) level of hookah cessation within 9 months of the intervention.

*The measurement of secondary outcomes* (1) Comparison of the frequency of hookah consumption before and after the intervention for those who did not stop hookah smoking, (2) point prevalence of study participants (no hookah use during the past 7 days) at the end of the intervention and at 3, 6 and 12 month follow-up, (3) comparison of the number of hookah cessation attempts before and after the intervention, (4) participants’ tendency to stop hookah 6 months after the intervention, (5) rate of cessation as a result of intervention among the study participants after 6 months, and (6) rate of cessation as a result of intervention among the study participants after 12 months.

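### The 80% power is calculated for a self-efficacy score that is not a named outcome, so power for the primary outcome, hookah cessation, is neither stated nor derivable

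*Protocol article*

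**What the plan says.** The Sample size section uses the formula for comparing two groups with "d = 1, s1 = 2.55 and s2 = 2.38". It identifies these values as coming from "self-efficacy three months after training in both intervention and control groups" in a cited earlier study. With α = 0.05 and β = 0.2 it concludes that "the sample size will be calculated as 96 individuals in each group", and then that "by taking 10% sample drop into account, the number of samples in each group will be estimated as 106 individuals".

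The section Step 6: Planning the evaluation gives the purpose of the quasi-experimental study as "evaluating the effectiveness of designed educational intervention on smoking cessation/reduction rate among women". The Instrument section lists four primary outcomes, all of one kind: "level of hookah cessation immediately after the intervention", then the same at 3, 6 and 9 months, for example "level of hookah cessation within 6 months of the intervention". The six secondary outcomes cover consumption frequency in those who continue, 7-day abstinence, quit attempts, the tendency to stop, and cessation rates after 6 and 12 months.

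Self-efficacy is mentioned only in the Sample size section. No cessation rate for either group, and no target difference in cessation, is given anywhere.

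**The concern.** A power statement holds only for the variable, difference and variability put into it. Here all three come from a self-efficacy scale in another study, while the trial is to be judged on cessation. A reader who meets the 80% next to a cessation objective will take it as the chance of detecting a worthwhile effect on quitting, and nothing in the document supports that.

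What is at stake is interpretation. If the arms do not differ significantly on cessation, nobody can say from the protocol which difference in quitting the trial was able to detect, so a null result could not be weighed. The units are a further difficulty. According to the Instrument section, the questionnaire is still to be built from the study's own matrix of objectives, so a difference of 1 with SDs near 2.5 has not been shown to mean anything on it.

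**Working it through.** **1. Reproducing the plan's own figure.** Inputs from the Sample size section: d = 1, s1 = 2.55, s2 = 2.38, α = 0.05, power 80%. Sidedness is not stated.

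Formula for two independent means: n = (s1² + s2²)(z₀.₉₇₅ + z₀.₈₀)² / d².

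- s1² + s2² = 6.5025 + 5.6644 = 12.1669.
- With z values 1.960 and 0.8416: n = 12.1669 × (2.8016)² / 1 = 95.5, rounded up to 96.
- A one-sided test would give 76, so the calculation was two-sided.
- Dropout: 96 × 1.1 = 105.6, hence 106. Dividing by 0.9 gives 106.7, hence 107; the difference is immaterial.

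The 96 is therefore fully explained by the self-efficacy inputs, and no cessation quantity enters it.

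**2. What 96 per arm means for cessation.** The document gives no quit rate, so control rates of 5%, 10% and 20% are assumed. Three further assumptions are made:

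- Cessation is read as a proportion.
- The test is two-sided at 0.05 with 96 evaluable women per arm.
- Women are treated as independent.

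Formula: power = Φ{[Δ − 1.96·√(2p̄(1 − p̄)/n)] / √[(p1(1 − p1) + p2(1 − p2))/n]}, with Δ = p2 − p1 and p̄ the mean of p1 and p2.

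Worked case, 10% vs 20%:

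- p̄ = 0.15, and √(2 × 0.15 × 0.85/96) = 0.0515.
- √[(0.09 + 0.16)/96] = 0.0510.
- (0.10 − 1.96 × 0.0515)/0.0510 = −0.02, so power is 49%.

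| Assumed control rate | Intervention rate for 80% power | Difference (points) | Power, 10-point gain | Power, 15-point gain |
|---|---|---|---|---|
| 5% | 17.8% | 12.8 | 64% | 89% |
| 10% | 25.3% | 15.3 | 49% | 79% |
| 20% | 38.3% | 18.3 | 36% | 65% |

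For 80% power, a 10-point gain would need 141, 199 or 294 per arm at these control rates, and a 15-point gain 76, 100 or 138.

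**3. Direction of the remaining error.** The Recruitment section assigns whole health centres, two to each arm. If women within a centre resemble each other, true power is lower than in the table. No intracluster correlation is given, and with two centres per arm a simple deflation of n would not be reliable, so no clustered figure is offered here.

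**The case against.** Several points can fairly be made for the plan.

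- **Self-efficacy may yet be measured.** Step 6 says that determinants and change objectives will be evaluated, and the questionnaire is to cover change objectives. The t-tests and path analysis under Statistical analysis would suit a continuous determinant score. This stands: a reader might infer that self-efficacy has no place in the trial, and the document does not support that. It supports only that self-efficacy is not a named primary or secondary outcome.
- **The scale may carry over.** Nothing excludes adopting an existing self-efficacy scale. This also stands, so the units are not shown to carry over; it cannot be said that they do not.
- **Cessation may not be binary.** The primary outcomes speak of a level, and Step 6 joins cessation with reduction. All women smoke at entry (Inclusion criteria), the secondary outcomes speak of rates and 7-day abstinence, and logistic regression is planned. A proportion is thus the likely reading, but it is never defined. If the outcome were continuous, the self-efficacy inputs still would not apply.
- **The protocol does not explicitly claim 80% power for cessation.** That is true. But it is the only power given, and it stands as the justification for the size of a trial whose primary outcomes are cessation.

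None of this supplies a power statement for cessation. Nor is this a detail left to an analysis plan: the article states a basis for its sample size, and that basis does not match its own primary outcomes.

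**Conclusion.** The point holds. The sample size is correctly computed, but for a variable outside both outcome lists. The stated 80% does not apply to the primary outcome, and power for cessation cannot be derived from the document.

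A reader might go further and infer that the trial is underpowered, or that realistic programme effects would be missed. The document does not support this, because it gives no quit rate and no expected effect. Under the assumptions above, 96 per arm is adequate for large gains: a 15-point gain has 89% power from a 5% control rate and is close to target (79%) from 10%. It is weak for a 10-point gain, at 64%, 49% and 36% from control rates of 5%, 10% and 20%. These figures rest on assumed control rates, a binary reading of cessation and independence between women. They are illustrations, and optimistic ones given allocation by centre.

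**What to change.** In the Sample size section:

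1. State that the 80% refers to a self-efficacy difference only.
2. Name one of the primary time points and, for the cessation proportion at that point, give the assumed control quit rate with a range (for instance 5% to 20%) and the difference detectable with 96 evaluable women per arm.
3. Note that assigning two centres to each arm lowers the true power. If an intracluster correlation is used, label it as an assumption and show a range.
4. Claim 80% power for cessation only if that calculation supports it.

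This is a change of text, and enrolment need not change. The cost is a less favourable power statement. If the sponsor then wants 80% power for a smaller gain, that is a separate decision about enrolment.

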#### Recruitment

The random method will be used for sampling. First, four comprehensive health centers will be randomly selected in Bandar Abbas, from which, two will be randomly assigned to the intervention group and two to the control group. The number of samples from each center will be determined according to the population covered by the center. To select eligible individuals, SD will randomly select a family record belonging to the population covered by the selected comprehensive health centers.

Then, to select other people, the researcher will visit all houses on the right side of the first selected record. After identifying the samples and obtaining informed consent from them, the phone number of all samples will be obtained for correspondence.

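### The 96 women per group and the 80% power assume independent individuals, but whole centres are allocated, two per arm, and a valid test on that design cannot reach 80%

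*Protocol article*

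**What the plan says.** The Sample size section says that "the sampling formula in comparative studies will be used", with the inputs "d = 1, s1 = 2.55 and s2 = 2.38, respectively". These are attributed to another study's results for "self-efficacy three months after training in both intervention and control groups". Alpha is 0.05 and beta 0.2. The result is that "the sample size will be calculated as 96 individuals in each group", and then "by taking 10% sample drop into account, the number of samples in each group will be estimated as 106 individuals". Dropout is the only inflation applied.

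The Recruitment section describes the allocation: "four comprehensive health centers will be randomly selected in Bandar Abbas", of which "two will be randomly assigned to the intervention group and two to the control group". Each centre's share of the sample depends on the population it covers. Women are sampled within a centre through a randomly chosen family record and then the houses next to it.

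The Statistical analysis section names independent and paired t-tests, path analysis and logistic regression, and mentions no term for centre.

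**The concern.** The unit allocated is the centre, while the sample size treats the woman as the unit. Women in one centre share a neighbourhood, a health service and, in the intervention arm, group training sessions, so their outcomes are likely to be correlated. Any such correlation makes 96 women from two centres worth fewer than 96 independent women. Separately, with two centres per arm there are only four units from which to judge variation between centres, which leaves 2 degrees of freedom for a test that respects the allocation.

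The 80% figure is the only justification given for the size of the trial. If it is wrong, a null result from a valid analysis would be read as a well-powered negative when it is close to uninformative. If the correlation is ignored in the analysis instead, a positive result may be spurious.

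**Working it through.** **Inputs from the protocol article.** d = 1, s1 = 2.55, s2 = 2.38, alpha 0.05, power 80%, 96 per group (Sample size); four centres, two per arm (Recruitment). Mean evaluable women per centre: 96/2 = 48.

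**Assumptions.** The article does not say whether alpha is one- or two-sided; two-sided is used because it reproduces the stated figure (one-sided would give 76). Centres are taken as equal in size, although the plan sizes them by population; unequal sizes would lower power further. The ICC is not given, so 0 to 0.05 is shown.

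**1. Reproduce the plan's figure.**

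s1² + s2² = 6.5025 + 5.6644 = 12.1669

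n = (1.960 + 0.842)² × 12.1669 / 1² = 95.5, rounded up to 96. Power at 96 per group is 80.2%.

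96 × 1.10 = 105.6, rounded up to 106. (Dividing by 0.90 would give 107; the difference is immaterial.)

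The 96 is therefore the independent-individuals figure with a design effect of exactly 1. Nothing in it can be a hidden allowance for clustering.

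**2. Power with two centres of 48 per arm.**

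Design effect DE = 1 + (48 − 1) × ICC; effective n = 96/DE; SE² = 12.1669 × DE/96.

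Normal-approximation power = Φ(1/SE − 1.96). Centre-level test: non-central t with 2(2 − 1) = 2 df, non-centrality 1/SE, critical value 4.303.

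| ICC (assumed) | DE | Effective n per arm | 1/SE | Power, normal approx. | Power, t on 2 df |
|---|---|---|---|---|---|
| 0 | 1.00 | 96 | 2.81 | 80% | 35% |
| 0.001 | 1.05 | 92 | 2.75 | 78% | 34% |
| 0.01 | 1.47 | 65 | 2.32 | 64% | 27% |
| 0.02 | 1.94 | 49.5 | 2.02 | 52% | 22% |
| 0.05 | 3.35 | 29 | 1.53 | 34% | 15% |

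If all 106 recruited per arm were analysed (53 per centre), ICCs of 0.01, 0.02 and 0.05 would give 67%, 54% and 34% by the normal approximation, and 28%, 23% and 16% on 2 df.

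**3. Would more women in the same four centres help?** However many women are recruited, SE² cannot fall below 12.1669 × ICC/2.

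- Normal approximation: 80% power needs 1/SE = 2.802, so it is out of reach once the ICC exceeds 2/(12.1669 × 2.802²) = 0.021.
- Test on 2 df: 80% power needs 1/SE = 5.653, so the limit is 2/(12.1669 × 5.653²) = 0.005. At an ICC of zero it would take 12.1669 × 5.653² ≈ 389 women per arm.

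**4. What if centre is ignored in the analysis?** The type I error of the unadjusted test is about 2 × [1 − Φ(1.96/√DE)], which is 11%, 16% and 28% at ICC 0.01, 0.02 and 0.05. It would reject about 76%, 73% and 68% of the time at d = 1, but not at a 5% error rate.

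**5. Same women, more centres.** With six centres of 16 per arm, DE = 1 + 15 × ICC = 1.15, 1.30 and 1.75. On 2(6 − 1) = 10 df, power is about 66%, 60% and 48%, and 72% at an ICC of zero.

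**The case against.** Five points can be made for the plan or against the force of this criticism.

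- **The power figures rest on an ICC the article does not give, and the lowest rest on the choice of a 2-df test.** This is true. By the normal approximation 96 per arm still has 78% power at an ICC of 0.001. But that approximation treats the between-centre variance as known, and four centres cannot supply it. A test that estimates it from those centres has at most 35% power at any ICC.
- **The plan names individual-level tests, so a false positive is the nearer danger, not a misread null.** This stands as an addition. As written, the analysis would keep its rejection rate by giving up the 5% error rate. That does not rescue the 80%, which is stated for alpha 0.05.
- **The inputs are for self-efficacy, while the primary outcomes are levels of hookah cessation.** This is also true. All the power figures here, like the plan's own, concern self-efficacy and say nothing direct about cessation. It is a further weakness of the calculation and does not excuse the missing design effect.
- **Six centres per arm still falls short of 80%, and the article does not say how many centres the city has.** This stands. The spread is a partial recovery whose feasibility is unknown.
- **The study is called quasi-experimental, and a fuller analysis plan may deal with clustering.** The label does not matter while whole centres are allocated. A later analysis plan can change the test but cannot add centres after allocation, and a valid test is what exposes the low power.

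**Conclusion.** The point holds. The arithmetic of 96 is right, but the formula does not match the allocation, so the stated 80% is wrong for this design. At assumed ICCs of 0.01 to 0.05, power for the plan's own difference and SDs is about 64% down to 34% if the small number of centres is ignored, and 27% down to 15% with a test that respects it. The ceiling for that test with 96 per arm is 35%, at an ICC of zero. The exact loss depends on the unknown ICC and on equal centre sizes; the failure to reach 80% with a valid centre-level test does not. It must be corrected before centres are allocated, because the number of centres cannot be repaired afterwards.

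**What to change.** Rewrite the Sample size section to give the assumed ICC and its source, the design effect for 48 to 53 women per centre, and the power actually obtained with two centres per arm. Delete the 80% claim. State that the analysis will respect allocation by centre, so that the restated power and the test belong together.

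This costs only rewording and a less favourable stated power.

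If more centres are available, spread the same 96 evaluable women per arm over more of them before allocation; six of 16 per arm gives the 66%, 60% and 48% shown above. This needs no extra participants but adds travel and training venues. It will not restore 80%, because 96 independent women per arm only just reach it, so a design meant to have 80% power needs both more centres and more women. If only four centres are feasible, present the evaluation as having low power and do not read a null result as evidence of no effect.
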